## 7.4. Safety Assessments

Assessments will be performed at three stages: 1) prior-treatment screening to assess the inclusion and exclusion criteria (once from days -7 to -1 before medication); 2) treatment evaluation to determine the response and adjustment of medication maintenance (twice weekly for week 1, once weekly from week 2 to 6, once every 2 weeks from week 7 to 12, and once every month from week 13 to 24 after the start of medication n); 3) post-treatment evaluation for follow-up (every 2 months for 6 months).

### 7.4.1. Adverse Events

Adverse events (AE) will be monitored from the time the subject signs the ICF. Subjects will be instructed to report all AEs during the study and will be assessed for the occurrence of AEs throughout the study. In order to avoid bias in eliciting AEs, subjects will be asked general, nonleading questions such as "How are you feeling?" All AEs (serious and nonserious) must be recorded on the source documents and eCRFs regardless of the assumption of a causal relationship with the study drug.

**7.4.1.1. Definitions**

For the purposes of this Protocol, an AE is defined as any untoward medical occurrence associated with the use of a drug in humans, whether or not considered drug related that occurs after a subject provides informed consent. Abnormal laboratory values or test results occurring after informed consent constitute AEs only if they induce clinical signs or symptoms, are considered clinically meaningful, require therapy (eg, hematologic abnormality that requires transfusion), or require changes in the study drug(s).

**7.4.1.2. Reporting**

Adverse events that begin or worsen after informed consent should be recorded on the Adverse Events form of the eCRF. Conditions that were already present at the time of informed consent should be recorded on the Medical History form in the eCRF. Monitoring for the occurrence of new AEs should be continued for at least 30 days after the last dose of study drug. Adverse events (including laboratory abnormalities that constitute AEs) should be described using a diagnosis whenever possible rather than by individual underlying signs and symptoms. When a clear diagnosis cannot be identified, each sign or symptom should be reported as a separate AE.

The term “disease progression” should be recorded as an AE/SAE itself only if there are no other identifiable AEs/SAEs associated with the disease progression at the time of reporting. For events associated with disease progression, the relevant signs and symptom should be reported using a diagnosis whenever possible, rather than the individual underlying signs and symptoms. When a clear diagnosis cannot be identified, each sign or symptom should be reported as a separated AE. If the events

resulting from disease progression meet the criteria for an SAE (eg, resulted in hospitalization, a life-threatening event, or death), the specific event(s) should be reported as an SAE(s). In both cases (ie, AEs or SAEs related to disease progression), for each event it should be indicated whether the event (diagnosis or signs and symptoms) is related to disease progression.

The severity of AEs will be assessed using CTCAE v4.0 Grades 1 through 5. If an event is not classified by CTCAE, the severity of the AE will be graded according to the scale below to estimate the grade of severity.

| **Grade 1** | Mild; asymptomatic or mild symptoms; clinical or diagnostic observations only; intervention not indicated. |
| --- | --- |
| **Grade 2** | Moderate; minimal, local, or noninvasive intervention indicated; limiting age-appropriate activities of daily living. |
| **Grade 3** | Severe or medically significant but not immediately life-threatening; hospitalization or prolongation of hospitalization indicated; disabling; limiting self-care activities of daily living. |
| **Grade 4** | Life-threatening consequences; urgent intervention indicated. |
| **Grade 5** | Death due to AE |

The occurrence of AEs should be sought by nondirective questioning of the subject during the screening process after signing the ICF and at each visit during the study. Adverse events may also be detected when they are volunteered by the subject during the screening process or between visits, or through physical examination, laboratory test, or other assessments. To the extent possible, each AE should be evaluated to determine:

- The severity grade (CTCAE Grade 1 to 5).
- Whether there is at least a reasonable possibility that the AE is related to the study

treatment: suspected (yes) or not suspected (no).

- The start and end dates, unless unresolved at final follow-up.
- The action taken with regard to study drug.
- The event outcome (eg, not recovered/not resolved, recovered/resolved, recovering/resolving, recovered/resolved with sequelae, fatal, unknown).
- The seriousness, as per serious adverse event (SAE) definition.

Unlike routine safety assessments, SAEs are monitored continuously and have special reporting requirements. All AEs should be treated appropriately. If an AE is treated with a concomitant medication or nondrug therapy, this action should be recorded on Adverse Event form and the treatment should be specified on the Prior/Concomitant Medications or Procedures and Non-Drug Therapy form in the eCRF.

Once an AE is detected, it should be followed until it has resolved or until it is judged to be permanent; assessment should be made at each visit (or more frequently if necessary) of any changes in severity, the suspected relationship to the study drug, the interventions required to treat the event, and the outcome.

When the severity of an AE changes over time for a reporting period (eg, between visits), each change in severity will be reported as a separate AE until the event resolves. For example, 2 separate AEs will be reported if a subject has Grade 1 diarrhea, meeting the definition of an AE, that lasts for 3 days before worsening to a Grade 3 severity. The Grade 1 event will be reported as an AE with a start date equal to the day the event met the Grade 1 AE definition and a stop date equal to the day that the event increased in severity from Grade 1 to Grade 3. The Grade 3 event will also be reported as an AE, with the start date equal to the day the event changed in intensity from Grade 1 to Grade 3 and a stop date equal to the day that the event either changed severity again or resolved. For analysis purposes, this will be considered 1 AE for this subject, and the highest reported severity will be used.

**7.4.1.3. Laboratory Test Abnormalities**

Laboratory abnormalities that constitute an AE in their own right (considered clinically meaningful, induce clinical signs or symptoms, require concomitant therapy, or require changes in study drug) should be recorded on the Adverse Event form in the eCRF. Whenever possible, a diagnosis rather than a symptom should be provided (eg, "anemia" instead of "low hemoglobin"). Laboratory abnormalities that meet the criteria for AEs should be followed until they have returned to normal or an adequate explanation of the abnormality is found. When an abnormal laboratory test result corresponds to a sign or symptom of a previously reported AE, it is not necessary to separately record the laboratory test result as an additional event. Laboratory abnormalities that do not meet the definition of an AE should not be reported as AEs. A Grade 3 or 4 AE does not automatically indicate an SAE unless it meets the definition of serious, and/or per the investigator's discretion. A dose modification for the laboratory abnormality may be required and should not contribute to the designation of a laboratory test abnormality as an SAE.

### 7.4.2. Serious Adverse Events

**7.4.2.1. Definitions**

An SAE is defined as an event that meets at least 1 of the following criteria:

- Is fatal or life-threatening.
- Requires inpatient hospitalization or prolongation of existing hospitalization, unless hospitalization is a result of:
- A routine treatment or monitoring of the studied indication not associated with any deterioration in condition.
- An elective or preplanned treatment for a pre-existing condition that is unrelated to the indication under study and has not worsened since signing the ICF.
- A treatment on an emergency outpatient basis for an event not fulfilling any of the definitions of a SAE and not resulting in hospital admission.
- Any social reasons and respite care, in the absence of any deterioration in the subject's general condition.
- Results in persistent or significant disability, incapacity, or a substantial disruption of a person's ability to conduct normal life functions.
- Constitutes a congenital anomaly or birth defect.
- Is considered to be an important medical event or a medically significant event that may not result in death, be immediately life-threatening, or require hospitalization but may be considered serious when, based upon appropriate medical judgment, the event may jeopardize the subject or may require medical or surgical intervention to prevent 1 of the outcomes listed above.

**7.4.2.2. Reporting**

To ensure subject safety, every SAE, regardless of suspected causality (including events that may not be associated with the study drug[s] but may be associated with a study procedure or disease progression), unless otherwise specified by the Protocol, occurring after the subject has signed the ICF and up to the last study visit, or up to 30 days after the subject has stopped study treatment, whichever is later, must be reported to the sponsor (or designee) within 24 hours of learning of its occurrence. Any SAEs occurring more than 30 days after the last dose of study drug should be reported to the sponsor, or its designee, only if the investigator suspects a causal relationship to the study drug. An SAE occurring at a different time interval or otherwise considered completely unrelated to a previously reported SAE should be reported separately as a new event. Previously planned (ie, before providing informed consent) surgeries should not be reported as SAEs unless the underlying medical condition worsens over the course of the study.

Information about all SAEs is collected and recorded on the Adverse Event form of the eCRF. The investigator must assess and record the causal relationship of each SAE to each specific study drug (ruxolitinib and the corticosteroid during the time it is given).

The investigator must also complete the Serious Adverse Event Report Form, and send the completed and signed form to the sponsor or designee within 24 hours of becoming aware of the SAE. The investigator must provide a causality assessment, that is, assess whether there is at least a reasonable possibility that the SAE is related to the study treatment: suspected (yes) or not suspected (no).

The contact information of the sponsor's study-specific representatives is listed in the

investigator manual provided to each site. The original copy of the SAE Report Form and the confirmation sheet must be kept at the study site.

Investigational site personnel must report any new information regarding the SAE within 24 hours of becoming aware of the information in the same manner that the initial SAE Report Form was sent. Follow-up information is recorded on an amended or new SAE Report Form, with an indication that it is follow-up to the previously reported SAE and the date of the original report. The follow-up report should include information that was not provided on the previous SAE Report Form, such as the outcome of the event (eg, resolved or ongoing), treatment provided, action taken with study drug because of the SAE (eg, dose reduced, interrupted, or discontinued), or subject disposition (eg, continued or withdrew from study participation). Each recurrence, complication, or progression of the original event should be reported as follow-up to that event, regardless of when it occurs.

### 7.4.3. Physical Examination

The targeted physical examination will be a symptom-directed evaluation conducted by the investigator or a medically qualified designee. The targeted physical examination will include height (screening only) and assessment(s) of the body systems or organs, as indicated by subject symptoms, AEs, or other findings. Clinically notable abnormalities that are considered clinically significant in the judgment of the investigator are to be reported as AEs.

### 7.4.4. Vital Signs

Vital sign measurements include blood pressure, pulse, respiratory rate, body temperature, and body weight. Blood pressure and pulse will be taken with the subject in the recumbent, semirecumbent, or sitting position. Clinically notable abnormalities that are considered clinically significant in the judgment of the investigator are to be reported as AEs.

### 7.4.5. ECOG Performance Status

ECOG performance status (Table 2) will be assessed at screening and other study visits. Performance status must be assessed by a medically qualified individual and recorded in the eCRF.

**Table 2: ECOG Performance Status Grades**

| **Grade** | **Performance Status** |
| --- | --- |
| **0** | Fully active, able to carry on all predisease performance without restriction. |
| **1** | Restricted in physically strenuous activity but ambulatory and able to carry out work of a light or sedentary nature, eg, light house work, office work. |
| **2** | Ambulatory and capable of all self-care but unable to carry out any work activities. Up and about more than 50% of waking hours. |
| **3** | Capable of only limited self-care, confined to bed or chair more than 50% of waking hours. |
| **4** | Completely disabled. Cannot carry on any self-care. Totally confined to bed or chair. |
| **5** | Dead. |

### 7.4.6. Laboratory Assessments

Blood draws for laboratory assessments will occur at study visits. Blood draws will be completed before the subject receives the morning dose of study drug.

All laboratory assessments will be performed at a local (site) laboratory using institutional best practices. Results and normal reference ranges will be entered into the eCRF.

**7.4.6.1. Chemistry**

All chemistry panel assessments will be performed at a local (site) laboratory from blood samples collected using institutional best practices before administration of study drug. Results and normal reference ranges will be entered into the eCRF.

**7.4.6.2. Hematology**

Hematology assessments, including complete blood count with differential, will be performed at a local (site) laboratory using institutional best practices before administration of study drug. Results and normal reference ranges will be entered into the eCRF.

**7.4.6.3. Pregnancy Testing**

A serum pregnancy test will be required for all women of childbearing potential during screening and at the EOT visit. Urine pregnancy tests will be conducted every 28 days. Urine pregnancy tests will be performed locally. If a urine pregnancy test is positive, the results should be confirmed with a serum pregnancy test.

If the serum pregnancy test is negative after a urine test was positive, the investigator will assess the potential benefit/risk to the subject and determine whether it is in the subject's best interest to resume study drug and continue participation in the study.

**7.4.6.4. Hepatitis Screening**

Subjects with active HBV or HCV infection that requires treatment or who are at risk for HBV reactivation are excluded from the study. At risk for HBV reactivation is defined as hepatitis B surface antigen positive or anti–hepatitis B core antibody positive. Prior test results obtained as part of standard of care before allo-HSCT confirming that a subject is immune and not at risk for reactivation (ie, hepatitis B surface antigen negative, surface antibody positive) may be used for purposes of eligibility, and tests do not need to be repeated. Subjects with prior positive serology results must have negative polymerase chain reaction results. Subjects whose immune status is unknown or uncertain must have results confirming immune status before enrollment.

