## 3.2. Subject Exclusion Criteria

1. Has received more than one allogeneic stem cell transplant.

2. Female patients with pregnant or breast-feeding.

3. Has Acquired Immune Deficiency Syndrome (AIDS), or hepatitis B/C infection, uncontrolled bacterial, fungal, or viral infections.

4. Allergies to ruxolitinib.

5. Vital organ dysfunction unrelated to GVHD, including persistent bilirubin abnormalities or severe heart and respiratory diseases.

6. Relapse of the primary disease or graft rejection after transplantation.

7. Presence of GVHD overlap syndrome.

8. Presence of cGVHD or associated clinical signs or DLI-induced acute GVHD or interferon.

9. Previous history of JAK1/2 inhibitor treatment after transplantation, except JAK inhibitors administered before the transplantation.

10. absolute neutrophil count (ANC) <0.5×10^9^/L or platelet count (PLT) < 20×10^9^/L

11. Serum creatinine > 2.0 mg/dL or creatinine clearance < 40 mL/min measured or calculated by Cockroft-Gault equation.

12. Patients with poor compliance should not be included in the study based on the judgment of the research team, for example if they refused to take medicine at will many times during the previous treatment.

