# APPENDIX A. Table of Assessments

## Table 1: Schedule of Assessments

| Visist Day  Item | Sceening | D1 | D3 | D7 | D14 | D21 | D28 | D35 | D42 | D49 | D56 | D100 | D180 | +3m | +4.5m | +6m | +9m | +12m | +18m | +24m | +36m |
| --- | --- | --- | --- | --- | --- | --- | --- | --- | --- | --- | --- | --- | --- | --- | --- | --- | --- | --- | --- | --- | --- |
| Informed consent |  |  |  |  |  |  |  |  |  |  |  |  |  |  |  |  |  |  |  |  |  |
| I/E criteria |  |  |  |  |  |  |  |  |  |  |  |  |  |  |  |  |  |  |  |  |  |
| Contact IVRS |  |  |  |  |  |  |  |  |  |  |  |  |  |  |  |  |  |  |  |  |  |
| Demogragpy/disease history |  |  |  |  |  |  |  |  |  |  |  |  |  |  |  |  |  |  |  |  |  |
| Prior/concomitant medications |  |  |  |  |  |  |  |  |  |  |  |  |  |  |  |  |  |  |  |  |  |
| Supportive care medications |  |  |  |  |  |  |  |  |  |  |  |  |  |  |  |  |  |  |  |  |  |
| Physical examination |  |  |  |  |  |  |  |  |  |  |  |  |  |  |  |  |  |  |  |  |  |
| Vital signs |  |  |  |  |  |  |  |  |  |  |  |  |  |  |  |  |  |  |  |  |  |
| ECOG PS |  |  |  |  |  |  |  |  |  |  |  |  |  |  |  |  |  |  |  |  |  |
| acute GVHD grading |  |  |  |  |  |  |  |  |  |  |  |  |  |  |  |  |  |  |  |  |  |
| acute GVHD organ |  |  |  |  |  |  |  |  |  |  |  |  |  |  |  |  |  |  |  |  |  |
| acute GVHD response |  |  |  |  |  |  |  |  |  |  |  |  |  |  |  |  |  |  |  |  |  |
| cGVHD assessment |  |  |  |  |  |  |  |  |  |  |  |  |  |  |  |  |  |  |  |  |  |
| Chimerism/graft failure  assessment |  |  |  |  |  |  |  |  |  |  |  |  |  |  |  |  |  |  |  |  |  |
| EBV infection assessment |  |  |  |  |  |  |  |  |  |  |  |  |  |  |  |  |  |  |  |  |  |
| CMV infection assessment |  |  |  |  |  |  |  |  |  |  |  |  |  |  |  |  |  |  |  |  |  |
| Underlying disease relapse assessment |  |  |  |  |  |  |  |  |  |  |  |  |  |  |  |  |  |  |  |  |  |
| Ruxolitinib dose monitoring |  |  |  |  |  |  |  |  |  |  |  |  |  |  |  |  |  |  |  |  |  |
| Steroid dose monitoring |  |  |  |  |  |  |  |  |  |  |  |  |  |  |  |  |  |  |  |  |  |
| New acute GVHD therapies |  |  |  |  |  |  |  |  |  |  |  |  |  |  |  |  |  |  |  |  |  |
| Survival follow-up |  |  |  |  |  |  |  |  |  |  |  |  |  |  |  |  |  |  |  |  |  |

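### Section 7.4.6.4 makes anti-HBc positivity a ground for exclusion but leaves anti-HBc out of the results it accepts as proof that a patient is not at risk of HBV reactivation

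*Protocol*

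**What the plan says.** All the operative text is in one paragraph of the Protocol, Section 7.4.6.4 (Hepatitis Screening).

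- Exclusion: "Subjects with active HBV or HCV infection that requires treatment or who are at risk for HBV reactivation are excluded from the study".
- Definition: "At risk for HBV reactivation is defined as hepatitis B surface antigen positive or anti–hepatitis B core antibody positive".
- Waiver: pre-transplant standard-of-care results may be used if they confirm that the patient is "immune and not at risk for reactivation (ie, hepatitis B surface antigen negative, surface antibody positive) may be used for purposes of eligibility". The sentence ends by saying that tests need not be repeated.
- PCR: "Subjects with prior positive serology results must have negative polymerase chain reaction results".
- Unknown status: "Subjects whose immune status is unknown or uncertain must have results confirming immune status before enrollment".

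Exclusion criterion 3 in Section 3.2 is less specific. It names "hepatitis B/C infection, uncontrolled bacterial, fungal, or viral infections" and no serological marker. The Synopsis uses the same wording.

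**The concern.** The exclusion turns on two markers, and ruling risk out requires both to be negative. The waiver spells out what counts as confirmation, and anti-HBc is not in it. A site that works from the parenthesis could clear a patient for randomisation without the second marker ever having been measured.

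What is at stake is the protocol's own safety rule. Both arms receive methylprednisolone and cyclosporine (Sections 5.1.1 and 5.1.2), and one arm adds ruxolitinib, for which Section 1.4 warns of a possible increase in infections. That warning is general and does not name hepatitis B. Site staff determine eligibility (Section 4.4) at approximately 7 sites (Section 4.5.1), so consistent handling depends on this paragraph being unambiguous.

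**Working it through.** No arithmetic applies. The check applies the definition and the waiver to the same patients. The inputs are the definition, the waiver and the other sentences of Section 7.4.6.4, together with exclusion 3 in Section 3.2.

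Take a patient who is HBsAg negative and anti-HBs positive, so that the results listed in the waiver are met, and let anti-HBc vary.

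| Anti-HBc | Under the definition | Under the parenthesis | Do they agree? |
| --- | --- | --- | --- |
| Negative | Not at risk | Accepted | Yes |
| Positive | At risk, excluded | Listed results met | No, but the exclusion still bars the patient |
| Not on file | Risk cannot be ruled out | Listed results met | No, and this is the gap |

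Next, does any other text supply the missing result in the third row?

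1. The PCR sentence is triggered by a positive serology result. A missing anti-HBc result is not a positive one. If anti-HBs positivity were taken as the trigger, a negative PCR would still not show anti-HBc status, and the definition contains no PCR exception.
2. The sentence on unknown or uncertain status concerns immune status and does not name anti-HBc. On the 'ie' reading, the two listed results have already settled that status.
3. Exclusion 3 in Section 3.2 and the Synopsis speak only of hepatitis B/C infection and require no anti-HBc result.

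So no other sentence expressly requires the result.

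The neighbouring HIV paragraph (Section 7.4.6.5) is a useful comparison. Its waiver accepts earlier results that confirm the patient is HIV-negative, which is the status its exclusion depends on. The hepatitis waiver does not list everything its exclusion depends on.

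With core antibody negative added to the parenthesis, the rules agree in all three rows: the first patient is accepted, the second is not, and the third must be tested.

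**The case against.** The strongest defence is that the operative condition already includes anti-HBc. Earlier results count only if they confirm that the patient is not at risk, and that term is defined one sentence before. A file with no anti-HBc result cannot confirm it, and a reading that reconciles two adjacent sentences is normally preferred to one that sets them against each other. This reading is available, and it means that the 'ie' reading is not the only one. It does not make the wording sound, because 'ie' announces a full statement of what is meant and a site can reasonably stop there.

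The second defence rests on the word repeated. The waiver says that such results "may be used for purposes of eligibility, and tests do not need to be repeated". A test never done is not being repeated, so the sentence does not plainly waive a first anti-HBc test. That also stands. Equally, the paragraph does not plainly require one once the listed results are in hand.

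Third, the sentence on unknown or uncertain status might catch the patient. It is a partial safeguard at best, since it refers to immune status and not to reactivation risk.

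A reader might infer that the protocol opens enrolment to patients known to be anti-HBc positive. It does not: the exclusion and the definition both remain in force for them. A reader might also point to the lack of a hepatitis row in the Appendix A schedule. That shows nothing, because the table as available also has no rows for the chemistry, haematology, pregnancy and HIV tests that Section 7.4.6 requires.

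**Conclusion.** The point holds as an internal inconsistency of minor severity. The definition needs an anti-HBc result to rule risk out, the parenthesis does not ask for one, and no other sentence expressly does. On the plain reading of 'ie', a patient with no anti-HBc result on file can be accepted; on the reconciling reading that patient cannot. A safety exclusion should not depend on which reading a site adopts.

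It would go too far to conclude that ineligible patients will be enrolled. Actual harm would require a pre-transplant file with no anti-HBc result, a patient whose unmeasured result would be positive, and a site that relies on the parenthesis alone. The protocol does not show how often any of these occurs among the 198 planned patients, so the risk is possible, not demonstrated, and no count is offered. The consequence is limited to participant safety and uniform eligibility, with no effect on alpha, power or the between-arm comparison.

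**What to change.** In Section 7.4.6.4, amend the parenthesis to list three results: hepatitis B surface antigen negative, core antibody negative, surface antibody positive. A patient with no anti-HBc result on file is then tested before enrolment.

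The cost is one amended parenthesis and at most one serology result per patient where none is on file. The result must come back within the 2-day screening limit of Section 6.1; the Synopsis allows up to 28 days, so the shorter limit is the demanding case. Any patient then found anti-HBc positive is one the current definition already excludes, so the eligible population as defined does not shrink.

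A separate, optional clarification is whether the PCR sentence only adds a requirement or is meant as a route to enrolment for anti-HBc-positive patients with negative HBV DNA. The parenthesis change is right either way: anti-HBc would serve as the exclusion marker in the first case and as the trigger for PCR in the second.
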